## Introduction

The use of spinal fusion (SF) procedures has significantly increased over the past decade to stabilize the spine in degenerative, oncologic, and traumatic conditions (1). Despite advancements in spinal surgery, pseudarthrosis remains a concern, occurring in approximately 25–35% of procedures (2–6). Several factors influence fusion rates, including patient characteristics (e.g., age and osteoporosis) and treatment-related aspects (e.g., number of levels treated, use of instrumentation, interbody grafts, and surgical approach) (7). With the increase in aging population and the growing need for multilevel spinal fusion surgery, there is a demand for techniques that enhance SF success rates and reduce pseudarthrosis (8). While iliac crest autograft and local autograft (spinous processes/laminae) are considered the gold standard, their use is limited by supply constraints and associated complications (1, 9). Bone allografts serve as substitutes for autografts and can be combined with Vertebral Bone Marrow Aspirate (vBMA) instead of iliac crest bone marrow aspirate to enhance osteogenic properties (10–12). vBMA is readily accessible in spinal surgery during the preparation for pedicle screw insertion and contains ⁓70% more osteoprogenitor cells—derived from mesenchymal stem cells (MSCs)—than iliac crest aspirates (13, 14). Studies have also shown that MSCs from vBMA exhibit high expression levels of Bone Gamma-Carboxyglutamate Protein (BGLAP), Alkaline Phosphatase (ALPL), and Runt-Related Transcription Factor 2 (RUNX2) genes, which are key regulators of the mineralization process, along with specific Hox gene expression, which influences vertebral morphology (13–15). Furthermore, despite vertebrae being sites of high bone turnover and among the first affected by age-related osteoporosis, the biological characteristics of vBMA remain unaffected by donor age (16, 17). However, the primary limitations of vBMA use in spinal surgery include the lack of a standardized procedure and its liquid nature, which risks diffusion away from the implant site (18).

In 2018, our research group introduced a novel formulation of vBMA—the vBMA clot (19). MSCs derived from clotted vBMA demonstrated superior growth kinetics, increased expression of key growth factors (Transforming Growth Factor Beta, TGFβ; Vascular Endothelial Growth Factor A, VEGF-A; and Fibroblast Growth Factor 2, FGF2), enhanced differentiation potential toward osteogenic and chondrogenic lineages, and reduced expression of Pbx1 and Meis3 genes, which negatively regulate osteoblast development (20). These findings highlighted the superior biological properties of the cellular component within clotted vBMA. The use of clotted vBMA offers distinct advantages over whole and concentrated vBMA, eliminating the need for concentration or purification while providing enhanced stability at the graft site. Given the increasing prevalence of spinal surgery in elderly patients, we also investigated the impact of aging on vBMA clot properties (21). A 2022 study confirmed that donor age does not affect the biological potential of vBMA clot (21). Furthermore, key markers related to aging and cellular senescence were not negatively influenced by age (21). To further validate the clinical application of vBMA clot in SF procedures, a pilot clinical study was conducted at the IRCCS Istituto Ortopedico Rizzoli, involving 10 patients with degenerative spine diseases (Ethical Committee approval n. 587/2020/Sper). At the 12-month FU, the study reported a 100% interbody fusion success rate based on the Brantigan classification and increased bone density from 6 to 12 months postoperatively (13, 22). Patients also experienced significant improvements in the quality of life and health status, as evidenced by clinical scores [Oswestry Disability Index (ODI), Visual Analog Scale (VAS), and EuroQol-5 Level (EQ-5D-5L)] as early as 3 months post-surgery (13).

Despite these promising results, evidence of the true clinical benefits of this treatment strategy remains limited, and no high-level clinical studies have thoroughly investigated its advantages. Furthermore, the preclinical biological, anti-inflammatory, and antibacterial properties of this multifunctional bioscaffold remain underexplored.

A randomized clinical trial (RCT) evaluating the additional benefit of vBMA compared to allogeneic bone alone could provide definitive insights and help establish this combined therapeutic approach as a standard treatment option for patients undergoing SF surgery in the lumbar spine.

### Objectives and trial design

An RCT has been designed to evaluate the efficacy of autologous vBMA clots in SF procedures for patients with lumbar degenerative spine diseases. The study compares two groups: patients treated with autologous vBMA clots combined with bone allograft chips versus those receiving bone allograft chips alone (standard treatment). Additionally, the study assesses whether patient age and gender influence clinical outcomes.

As secondary objectives, this study aims to characterize platelet-specific parameters, cytokines/chemokines, growth factors, pro-inflammatory and anti-inflammatory markers, and MSCs that define the vBMA clot through molecular and cellular analyses. To further investigate its intrinsic biological potential, an advanced humanized three-dimensional (3D) *in vitro* SF model is developed. All experimental setups will consider age and gender differences, including an evaluation of their interactions.

Furthermore, the study examines the antibacterial properties of vBMA clot against common Gram-positive and Gram-negative bacteria associated with spinal infections, including methicillin-sensitive and methicillin-resistant *Staphylococcus aureus* and *Escherichia coli*. *In vitro* time-kill and bacterial adhesion assays are conducted to assess the ability of vBMA clot to inhibit bacterial growth as well as analyze the potential variations related to patient age and gender.

## Methods and analysis

### Study setting

This controlled RCT investigates patients undergoing SF surgery for degenerative spinal diseases (disc disease, lumbar spinal stenosis, grade I and II spondylolisthesis, etc.). The study compares clinical and radiological outcomes between two groups: patients treated with vBMA clot combined with allograft bone chips (Group 1–Experimental) and those treated with allograft bone chips alone (Group 2–Standard). All trial-related activities are conducted at the IRCCS Istituto Ortopedico Rizzoli (Bologna, Italy), a specialized orthopedic center for treating spinal diseases, in compliance with the European Union Clinical Trial Regulation and the Declaration of Helsinki.

### Patient and public involvement

Patient and public involvement (PPI) in clinical trials emphasizes collaboration between researchers and patients, ensuring that studies address patient-centered concerns and priorities. In recent times, PPI extends beyond trials, influencing healthcare resource allocation and research priorities worldwide. Continued and sustainable progress—such as that proposed in the present trial, which utilizes a multifunctional therapeutic strategy based on a safe, functional, and easy-to-use bioscaffold—relies on strong policies, historical awareness, and ongoing evaluation to maintain balance and effectiveness in this partnership.

### Eligibility criteria

The inclusion criteria are men or women aged between 18 and 80 years at the time of surgery and patients with radiologically diagnosed spinal disorders who are candidates for posterior SF involving ≤5 levels, either posterolateral or interbody fusion, with pedicle screw fixation, excluding cases with standalone posterolateral fusion.

The exclusion criteria include patients with systemic infections (e.g., HIV, HBV, or HCV); those with coagulation disorders; pregnant or breastfeeding women; those with oncological diseases; those with local infectious diseases (e.g., tuberculous spondylodiscitis and suppurative spondylodiscitis); a history of previous spinal surgery; those undergoing radiotherapy or chemotherapy; those with myeloproliferative disease; those receiving steroid therapies; those with untreated thyroid disorders; immunosuppressed patients; those with traumatic spinal conditions; and those with osteoporotic conditions affecting spinal integrity.

### Surgical procedures and interventions

During the screening phase, local specialized orthopedic medical staff assess the eligibility of potential participants. Once informed consent is obtained, an external investigator (not involved in the trial) assigns participants to one of the two groups:

Group 1 (Experimental): vBMA clot combined with allograft bone chips;Group 2 (Standard): allograft bone chips alone.

As previously mentioned, the allograft bone chips are supplied by the local Musculoskeletal Tissue Bank, while the vBMA is harvested from the vertebral pedicles during surgical site preparation for pedicle screw insertion. The procedure follows a conventional posterior approach for lumbar SF and utilizes standardized instrumentation. In detail, after pedicle screw placement, decompression of the cauda equina and nerve roots is achieved through hemilaminectomy and foraminotomy, if necessary. Bone tissue removed during site preparation for arthrodesis is considered surgical waste and is not combined with allogeneic bone chips. The assigned treatment—either vBMA clot combined with allograft bone chips or allograft bone chips alone—is applied to the laminae or hemilaminae and the transverse process on the contralateral side of the hemilaminectomy. On the hemilaminectomy side, foramino-arthrectomy is performed to insert the interbody fusion cage, if needed.

Since aspiration volume influences the concentration of progenitor cells in vBMA, a standardized approach is used to maximize the cell yield. A predetermined volume of bone marrow, as defined in the registered patent application, is aspirated from each pedicle involved in the surgery. After aspiration, vBMA is evenly divided into two sterile containers, clotted (clotting time: 15–20 min), and then used for the surgical procedure (Figure 1). For each vertebra, the assigned treatment is administered as follows:

Experimental group: clotted vBMA combined with 20 g of allograft bone chips per side (Figure 1);Standard group: 20 g of allograft bone chips per side (Figure 2).

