## Ethics and dissemination

### Research ethics approval and consent

Ethical approval was granted on 16 March 2023 by the local Ethics Committee (CE AVEC) (Protocol MORE_FOR_SPINE; Number 149/2023/Sper). All participants will provide informed written consent during their baseline outpatient medical examination with trained medical staff, before enrollment. Participation in the trial is entirely voluntary, and participants may withdraw at any time.

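### Interbody cage use is left open after the arm is assigned, to an operator who can be expected to know the arm, so the fusion comparison could be biased

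*Protocol article*

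**What the plan says.** All references are to the protocol article.

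- **Eligibility check** (Surgical procedures and interventions): "During the screening phase, local specialized orthopedic medical staff assess the eligibility of potential participants".
- **Consent** (Research ethics approval and consent): participants give "informed written consent during their baseline outpatient medical examination with trained medical staff, before enrollment".
- **Assignment** (Surgical procedures and interventions): "Once informed consent is obtained, an external investigator (not involved in the trial) assigns participants to one of the two groups".
- **Cage** (same section): on the hemilaminectomy side, "foramino-arthrectomy is performed to insert the interbody fusion cage, if needed". The article gives no criterion for need and does not say when need is decided. The step comes after pedicle screw placement in the description, and marrow is harvested while the pedicles are being prepared for the screws.
- **Included fusion types** (Eligibility criteria): candidates for posterior fusion, "either posterolateral or interbody fusion, with pedicle screw fixation, excluding cases with standalone posterolateral fusion".
- **Determinants of fusion** (Introduction): the treatment-related factors listed are "number of levels treated, use of instrumentation, interbody grafts, and surgical approach".
- **Primary outcome** (Outcomes): a radiologist unaware of the arm assigns a Brantigan grade for interbody fusion.
- **Primary model** (Statistical methods): logistic regression with age and gender. Other factors are optional, and cage use is not named.
- **Blinding**: stated for the radiologist, for the evaluator of patient-reported outcomes, and for data collection and analysis. It is not stated for the operator.

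**The concern.** Randomisation balances what is fixed before the arm is known. It does not protect against choices made afterwards by someone aware of the arm. Here one such choice, whether to place a cage, concerns a factor that the article itself says influences fusion.

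Two things are at stake. If cages are used more readily in one arm, the fusion difference mixes the effect of the clot with the effect of the cage. And because the primary scale grades interbody fusion, the choice may also decide which levels can be graded, so the set of graded levels could differ by arm. The blinded radiologist sees only the result of the operation and cannot correct either problem.

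**Working it through.** **1. Order of events.** Screening and eligibility check, then consent at the outpatient visit, then assignment, then surgery (pedicle preparation with marrow harvest, screw placement, decompression where required, graft, cage where required). Assignment therefore precedes the cage step. That the operator knows the arm by then is an inference: the clot is used in one arm only, is harvested earlier in the same operation and takes 15 to 20 minutes to form. Nothing in the article suggests that the operator is kept unaware.

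**2. The plan's own figure.** Inputs from Statistical methods: one-tailed Fisher's exact test, 95% confidence level, power 0.80, control fusion 70%, OR 4.8, 20% dropout.
- Control odds = 0.70/0.30 = 2.333. Experimental odds = 4.8 × 2.333 = 11.2. Experimental rate = 11.2/12.2 = 91.8%.
- Exact power reaches 0.802 at 46 per arm. 46/0.80 = 57.5, rounded up to 58. The stated 58 reproduces.
- Planned difference: 91 − 70 = 21 points on the stated percentages, or 91.8 − 70 = about 22 points on the OR.

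**3. Bias from unequal cage use, with no true clot effect.** The article gives neither the size of the cage effect nor any cage frequencies, so these are assumptions. Let *g* be the points of fusion that a cage adds, *d* the excess cage use in the experimental arm, and let half of the controls have a cage, with control fusion at 70%.
- Fusion without a cage = 0.70 − 0.5*g*.
- Experimental fusion = (0.70 − 0.5*g*) + (0.5 + *d*)*g* = 0.70 + *d* × *g*.
- Spurious difference = *d* × *g*, whatever the control share of cages.

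Chance of a one-sided Fisher p ≤ 0.05 when the clot does nothing:

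| *g* and *d* (points, either order) | Spurious difference | 46 per arm | 58 per arm |
|---|---|---|---|
| balanced | 0 | 3.05% | 3.32% |
| 10 and 10 | 1 point | 3.84% | 4.29% |
| 10 and 20 | 2 points | 4.80% | 5.50% |
| 10 and 30 | 3 points | 5.96% | 6.98% |
| 20 and 20 | 4 points | 7.35% | 8.77% |
| 20 and 30 | 6 points | 10.94% | 13.42% |
| 30 and 30 | 9 points | 18.72% | 23.45% |

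The range is 1 to 9 points. Among these cases, the false-positive rate first exceeds 5% at 3 points with 46 per arm and at 2 points with 58 per arm. If cages were used more in the control arm, the bias would have the opposite sign and hide a real effect.

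**4. Sections that do not fit together.** Eligibility criteria admits posterolateral or interbody fusion but rules out standalone posterolateral fusion. Surgical procedures and interventions allows an operation without a cage. Outcomes grades interbody fusion only. The article does not say whether a screw-fixed patient without a cage is included, or how such a patient is graded.

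**The case against.** The strongest reply is that the discretion may be smaller than it looks. The conditional wording may only mean that some patients or levels receive a cage and others do not, with the need settled before surgery. The full protocol is not shown and could fix this. Operators cannot be blinded to a graft of this kind, so some discretion is inherent. The model may take further factors, and Potential limitations already concedes bias from surgical technique and varied indications. No reason is given to expect cage use to differ by arm, and the bias is material only if both assumed inputs are sizeable.

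Much of this stands: the timing of the cage decision is inferred and the size is assumed. What it does not answer is that the stated sequence puts assignment before an open step that affects the primary outcome. Adding the cage actually used to the model would not repair this, because that is itself a choice made after assignment.

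A reader might go further and infer that a patient who receives no cage becomes ineligible after assignment, so that an operator could remove patients selectively by arm. The article does not support that. Eligibility is assessed at screening, the criterion speaks of candidates, and no rule for exclusion after assignment is stated. Nor is it clear that no cage means standalone posterolateral: that term could instead mean posterolateral fusion without screws.

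**Conclusion.** The concern holds as a weakness in the stated sequence. The arm is assigned before surgery, cage use is then open, and the operator can be expected to know the arm. An arm-related difference in cage use could bias the fusion rate and the set of gradable levels. Under the assumed ranges the spurious difference is 1 to 9 points against a planned 21 to 22. It is therefore unlikely to produce the whole planned effect, but it could raise the false-positive rate noticeably if both the cage effect and the imbalance are large. The conclusion rests on two inferences: that the operator knows the arm at the cage step, and that the need for a cage is not already settled before assignment. A shift in eligibility after assignment is not shown. The change is worth making because it is cheap and the bias could not be removed afterwards.

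**What to change.** - Reconcile Eligibility criteria, Surgical procedures and interventions, and Outcomes on which fusion types are included and how each is graded.
- Have the surgeon confirm eligibility and record the planned levels and the planned fusion type per level in the CRF before the arm is assigned or disclosed. Delaying disclosure until just before pedicle preparation would not be enough alone, since that still precedes the cage step. It is the recorded plan that protects.
- Keep every allocated patient in the analysis as randomised, whatever is done in surgery.
- Adjust the primary model for the planned fusion type recorded before allocation, not for the cage actually used.
- Report actual cage use and deviations from the recorded plan by arm.

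Who should receive a cage is a clinical matter and is not judged here. The cost is one extra CRF entry and holding assignment until that entry is complete. The number of patients is unchanged. If enrolment has begun, analysis as randomised and reporting of cage use by arm can still be adopted for all patients.

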**Figure 1 fig1:**
[figure not shown]
Schematic representation of vBMA combined with allogenic bone chips treatment (experimental group).

**Figure 2 fig2:**
[figure not shown]
Schematic representation of allogenic bone chip approach (standard group).

The total volume depends on the number of spinal segments involved, with a maximum of 200 g of allogeneic bone and a predetermined volume, as defined in the registered patent application, of vBMA for a five-level fusion. Any remaining vBMA is allocated for preclinical *in vitro* studies, as described in the “Outcomes” section (Figure 1).

Postoperative care, including physical therapy and the use of bracing, was not standardized and was left to the discretion of the treating physician according to the patient’s clinical condition and standard hospital practices.

### Outcomes

The primary outcome is to compare the two groups regarding the rate and duration of SF. Radiographic assessments are conducted preoperatively and at 1, 3, 6, and 12 months of FUs. To minimize exposure to ionizing radiation, computed tomography (CT) is performed only at 6 and 12 months, alongside x-rays. A diagnostic and interventional radiologist, blinded to group assignments, evaluates CT scans and x-rays, assigning interbody fusion grade according to the Brantigan classification (ranging from A to E, with E indicating the highest fusion rate) (22). The SF rate is analyzed over the FU period, considering variations due to age and gender differences.

The secondary outcomes include evaluating the pseudoarthrosis rate estimated using the Brantigan classification (22) and clinical outcomes. Moreover, since Brantigan (and other similar) classifications are visual qualitative scales affected by a lack of precise quantification, we provided a new quantitative analysis based on density calculated on CT images. The density of the selected region of interest (ROI) has been calculated and reported in Hounsfield Units (HU) for each study (baseline and follow-up controls). ROIs have been positioned within facet joint spaces of all vertebral levels of interest. Differential values in facet joint density have been reported by comparing baseline with follow-up controls to integrate the Brantigan scale (or help in cases of difficult grading selection), offering a quantitative and reliable tool. Measurements were performed using Picture Archive Communication System (PACS) software version 12.2.6.2000019.

Clinical outcomes include the following:Quality of life improvement was assessed through the VAS (0–10, with higher scores indicating more severe pain), the ODI (0–100, with higher scores indicating greater disability), and the SF-36, a standardized quality of life questionnaire based on patient self-assessment (23–25). These measures are administered at baseline (pre-surgery) and at 1, 3, 6, and 12 months postoperatively. Although patient-reported outcomes such as ODI, VAS, and SF-36 are typically self-reported, a blinded evaluator collected these outcomes to ensure standardization, consistency, and completeness of data across all participants. This approach minimizes potential biases related to symptoms and functioning reporting and enhances the overall reliability of the collected data.Postoperative complications are assessed through medical records, with complications classified as early (major and minor) or late based on their time of onset. Re-operation rates and implant removal were also recorded and analyzed as part of the clinical outcomes, indicating surgical complications and long-term treatment success. The results are analyzed for up to 12-month FUs.Laboratory parameters include routine blood tests, including red and white blood cell counts, platelet count, mean platelet volume, hemoglobin levels, etc., that are collected preoperatively and postoperatively. Additionally, any comorbidities and adverse events are systematically recorded.

Finally, coagulated vBMA from patients enrolled in the RCT is used to conduct several preclinical *in vitro* studies aimed at further investigating its characteristics, biological potential, and anti-inflammatory and antibacterial properties. These studies also evaluate age and gender differences and include an analysis of their interactions. Specifically, clotted vBMA is employed for the following:

Developing an advanced 3D *in vitro* model of SF: the vBMA clot is placed between allograft bone chips and cultured *in vitro* to evaluate cell viability, adhesion, distribution, and colonization of the cells within the vBMA clot in the allogeneic bone chips. Biological, molecular, histological, histomorphometric, and immunohistochemical analyses are performed;Characterizing, through immunoenzymatic assays and molecular techniques, the expression of platelet-derived growth factors, cytokines/chemokines, and osteotropic and angiogenic factors present in the coagulated vBMA can modulate bone formation, healing, regeneration, vascularization, and inflammation. Additionally, biological and molecular analyses are conducted to characterize the morphology, phenotype, and differentiation potential of MSCs present in the coagulated vBMA;Quantifying the antibacterial activity of vBMA can be achieved through microbiological tests using both Gram-positive and Gram-negative bacterial strains, employing microbiological techniques, cell biology methods, and scanning electron microscopy.

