After defining and managing the dataset, bivariate or multivariate analyses are carried out to evaluate relationships between variables. In the case of continuous data, the independent Student’s *t*-test and Wilcoxon rank-sum test are used to compare data between the two treatments for parametric and non-parametric data, respectively. Linear models are applied for regression analysis. In the case of categorical dichotomous data, Fisher’s Exact test or chi-squared test is used to compare proportions between the two treatments, and logistic models are applied for regression analysis. For non-dichotomous categorical data, the Mann–Whitney U-test or the Wilcoxon rank-sum test is used to compare ordered outcomes between the two treatments, and the Ordinal Least Squares, Cumulative Link, or Multinomial Logistic models are applied for regression analysis.

Since the variable of the primary outcome is dichotomous (fusion or no fusion), it is analyzed in relation to age (categorized) and gender through logistic regression models. Additional factors (e.g., follow-up time points) and covariates (e.g., platelet-derived growth factors) influencing spinal fusion may be included in the model. To combine covariates into a multiple logistic regression model, collinearity and predictive power are assessed. The results are reported as odds ratios (ORs) with corresponding 95% confidence intervals (CIs). The primary outcome is also assessed through appropriate stratifications of the population based on the presence or absence of specific comorbidities.

Given the longitudinal nature of FU data (e.g., VAS, ODI, and spinal fusion grading across multiple time points), repeated-measures ANOVA or linear mixed-effects models are applied to assess both within-subject (time) and between-group (treatment) effects, accounting for intra-subject correlation and missing data. This finding allows for a robust evaluation of changes over time and treatment efficacy.

Finally, after defining the most reliable models based on multiple criteria (e.g., Akaike Information Criterion, R^2^), diagnostic tools are used to evaluate model assumptions and identify potential influential observations. The same analysis process is implemented for the other regression models related to secondary outcomes, with appropriate diagnostics applied.

Data collection and statistical analysis are standardized and blinded.

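### If the arms are compared on the raw change in CT density, precision is generally lost against a baseline-adjusted model; the baseline reading must first be confirmed as pre-operative

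*Protocol article*

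**What the plan says.** In the protocol article, the Outcomes section introduces CT density because visual fusion grades lack precise quantification. Regions of interest are placed in the facet joint spaces, and density is "reported in Hounsfield Units (HU) for each study (baseline and follow-up controls"). The one derived summary named is a change: "Differential values in facet joint density have been reported by comparing baseline with follow-up controls to integrate the Brantigan scale". Its stated purpose is to supplement the grade "or help in cases of difficult grading selection), offering a quantitative and reliable tool".

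The same section says of imaging that "computed tomography (CT) is performed only at 6 and 12 months, alongside x-rays".

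Statistical methods does not mention HU by name. For continuous data it says "the independent Student’s *t*-test and Wilcoxon rank-sum test are used to compare data between the two treatments for parametric and non-parametric data, respectively", and then "Linear models are applied for regression analysis". For longitudinal data it says "repeated-measures ANOVA or linear mixed-effects models are applied to assess both within-subject (time) and between-group (treatment) effects", with VAS, ODI and fusion grading as examples. No baseline HU covariate appears anywhere.

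**The concern.** A raw change from baseline fixes the coefficient of the baseline reading at 1. That is the best coefficient only when the regression slope of follow-up HU on baseline HU is itself about 1. When the slope is lower, subtracting the full baseline adds noise, and a chance imbalance between the arms at baseline is over-corrected. A linear model with baseline HU as a covariate estimates the slope instead.

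A low slope is plausible here, though the article gives no data on it. The baseline reading is an unoperated facet joint. The follow-up reading is taken after screw placement, grafting and, on one side, possibly foramino-arthrectomy (Surgical procedures and interventions).

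HU is the only quantitative fusion measure in the trial. What is at stake is the precision of that comparison, not its validity.

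**Working it through.** **Inputs from the article.** There are 58 patients per arm including 20% drop-out (Statistical methods), so 58 × 0.8 = 46.4, or 46 evaluable. The figure reproduces. With 70% in the standard arm and an odds ratio of 4.8, the other arm is 0.70×4.8/(0.30+0.70×4.8) = 3.36/3.66 = 0.918. A one-tailed Fisher's exact test at 5% then has power 0.8015 with 46 per arm, and 46/0.8 = 57.5, rounded up to 58. That calculation concerns fusion and not HU; it supplies only the number of patients.

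**Assumptions (not in the article).** One HU value per patient and time point; a correlation r between baseline and follow-up HU; and k = baseline SD / follow-up SD. For power: a true effect of 0.6 follow-up SD, two-sided 5%.

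**Formulas**, in units of the follow-up variance:
- raw change: D = 1 + k² − 2rk
- baseline-adjusted: A = 1 − r² (ignoring one residual degree of freedom)
- share of variance saved: 1 − A/D, which is (1 − r)/2 when k = 1

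| k | r | D | A | Saved |
|---|---|---|---|---|
| 1 | 0 | 2.00 | 1.00 | 50% |
| 1 | 0.2 | 1.60 | 0.96 | 40% |
| 1 | 0.5 | 1.00 | 0.75 | 25% |
| 1 | 0.8 | 0.40 | 0.36 | 10% |
| 0.7 | 0.2 | 1.21 | 0.96 | 21% |
| 0.7 | 0.5 | 0.79 | 0.75 | 5% |
| 0.7 | 0.7 | 0.51 | 0.51 | 0% |

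The last row is zero because the slope r/k equals 1 there, so the raw change already uses the right coefficient. In the other direction, if the follow-up SD is 0.75 of the baseline SD, the saving is 57% at r=0.2 and 48% at r=0.5.

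**Simulation** with 46 per arm and k = 1 gave variance ratios A/D of 0.61, 0.75 and 0.91 at r = 0.2, 0.5 and 0.8. The formula gives 0.60, 0.75 and 0.90.

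**Power**, k = 1, 46 per arm, effect 0.6 SD (noncentral t):

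| r | Raw change | Adjusted |
|---|---|---|
| 0.2 | 61% | 83% |
| 0.3 | 67% | 85% |
| 0.5 | 81% | 91% |
| 0.7 | 96% | 98% |

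Follow-up HU alone gives 81%. With equal SDs, the raw change is therefore worse than ignoring baseline altogether when r is below 0.5. With k = 0.7 the gap is 74% against 83% at r=0.2, and it vanishes at r=0.7, where D = A.

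**The baseline reading.** Outcomes reports HU at baseline, yet limits CT to 6 and 12 months. For the patient-reported scores, the same section uses baseline to mean before surgery. The Introduction, by contrast, reports the pilot study's density result as a rise between 6 and 12 months. The article does not settle which scan supplies the baseline HU.

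**The case against.** The strongest case against has four parts.

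- **The analysis is not stated.** A reader might infer that the protocol commits to testing the arms on a raw difference. The text does not go that far. It says that the differentials are reported, in support of grading, and that HU itself is recorded at each scan. Statistical methods leaves linear and mixed models open, and an analysis plan that is not shown may name the covariate. This stands, and it makes the point conditional. It does not remove it: the article itself chooses the differential as its HU summary, and permission to use a model does not commit anyone to adjusting for baseline.
- **The covariate may not exist.** If there is no pre-operative CT, there is nothing to adjust for. If baseline means the 6-month scan, adjustment would condition on a reading that treatment may already have changed. This stands as a precondition. It does not favour the raw change, which needs the same baseline reading.
- **The size is assumed.** A reader might take 40% as typical or as an upper limit. It is neither: it belongs to r=0.2 with equal SDs. The saving is larger at r=0 or with a more variable baseline, and close to zero when the slope is near 1. Patients aged 18 to 80 may differ widely in bone density, which could raise r.
- **The consequence is small.** This stands. HU is supplementary.

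**Conclusion.** The point holds as a conditional, low-severity recommendation. If the arms are compared on the raw HU differential, the estimate is unbiased under randomisation, provided that the baseline is truly pre-operative. It is generally less precise than a baseline-adjusted estimate. Adjustment costs one degree of freedom and otherwise, in large samples, does no worse.

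The size depends wholly on assumed values. With equal SDs, and r from 0.8 down to 0.2, the variance saving runs from about 10% to 40%. With a baseline SD of 0.7 of the follow-up SD, and r from 0.7 down to 0.2, it runs from about 0% to 21%. The documents do not support reading this as bias, as an invalid result, or as a threat to the trial's main conclusion: the primary outcome is fusion or no fusion, and the sample size was set on that.

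**What to change.** 1. **Reconcile the baseline first.** State which scan supplies the baseline HU, and bring this into line with the sentence that limits CT to 6 and 12 months. The covariate must be a pre-operative reading, not the 6-month scan. If no pre-operative reading exists, neither the differential nor the adjustment is possible, and the text on differentials has to change.
2. **Then name the model.** Compare the arms on 6- and 12-month HU with a linear model (or a mixed model for both times) that has treatment arm and pre-operative HU as covariates. Report the adjusted mean difference with its 95% CI.
3. **Keep the raw differential** as a descriptive figure and as an aid to grading.

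If pre-operative readings are already held, the cost is one or two sentences before the data are analysed, with no new scans or readings. If they are not, this fix does not apply.
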